### Participant timeline {13}

Table 3 displays the schedule of enrollment, randomization, intervention, and assessments for the M2M study participants.

**Table 3 Tab3:**
[figure not shown]
Schedule of enrollment, randomization, intervention, and assessments for the M2M study participants

### Sample size {14}

Our conservative sample size and power calculations for the primary outcomes, which constitute a family of hypotheses [63], assume a two-sided overall family-wise error rate of 0.05 [64], 80% power, an analysis of covariance (ANCOVA)-based approach, and an attrition rate of 25% with 82 participants finishing the study. Under these assumptions, we will have 80% power to detect at least a minimally detectable difference (Cohen’s *d*) of 0.552. In these calculations, a conservative correlation of 0.6 between the baseline covariate and outcome is assumed, which is similar to a previous study by Froehlich-Grobe et al. [4].

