### Outcomes {12}

Primary and secondary outcomes include a set of physical assessments and self-report questionnaires and will be assessed at baseline and post 12-week intervention via the Zoom platform (teleassessments [34]) and REDCap electronic questionnaires. Assessors will be blinded to participant assignment, and allocation of the arm assignment will not be done until baseline testing is completed. The outcome measures included in this study were developed and validated in previous literature with adequate to excellent reliability. The primary outcomes include changes in cardiorespiratory fitness measured with resting heart rate [35] and the heart rate recovery test [36, 37] as well as muscle strength assessed with hand-held dynamometer [38–40] at post 12-week intervention. The secondary outcomes include changes in lower extremity function assessed with the Short Physical Performance Battery [41] and the Timed Up and Go tests [42–44], health-related quality of life measured using the NIH PROMIS 10 Global Health Items [45], social participation measured using the NIH PROMIS Ability to Participate in Social Roles and Activities Short Form 8a [45], and physical activity measured using the Godin Leisure Time Exercise Questionnaire [46–54] at post 12-week intervention. Table 2 summarizes all outcome measures and the corresponding data collection time points.

**Table 2 Tab2:** Outcome measures of the M2M study

Role	Variables	Outcome measures	Collection time points
**Primary outcomes**	Cardiorespiratory fitness	Resting heart rate [35] Heart rate recovery test [36, 37]	Baseline and 12 weeks
	Muscle strength	Hand-held dynamometer [38–40]	Baseline and 12 weeks
**Secondary outcomes**	Lower extremity function	Short physical performance battery [41] Timed up and go [42–44]	Baseline and 12 weeks
	Health-related quality of life	NIH PROMIS 10 Global Health Items [45]	Baseline and 12 weeks
	Social participation	NIH PROMIS Ability to Participate in Social Roles and Activities Short Form 8a [45]	Baseline and 12 weeks
	Physical activity	Godin Leisure Time Exercise Questionnaire [46–54]	Baseline and 12 weeks
**Mediators**	Program adherence	Percentage of # of attended eM2M sessions	12-week intervention period
	Group cohesion	Physical Activity Group Environment Questionnaire [55–57]	12 weeks
	Instructor support	Perceived Autonomy Support Scale for Exercise Settings [57, 58]	12 weeks
	Exercise self-efficacy	Exercise Self-efficacy Scale [59]	Baseline and 12 weeks

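### The detectable effect of 0.552 fits two primary tests under a single-step adjustment, but the protocol names three primary measures; over three, power at 0.552 can be as low as about 75%

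*Protocol article*

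**What the plan says.** The protocol article, Sample size {14}, describes "power calculations for the primary outcomes, which constitute a family of hypotheses" and goes on to "assume a two-sided overall family-wise error rate of 0.05". It adds 80% power, an ANCOVA approach, a baseline-to-outcome correlation of 0.6 and "an attrition rate of 25% with 82 participants finishing the study". From these it concludes that "we will have 80% power to detect at least a minimally detectable difference (Cohen’s *d*) of 0.552". It gives neither the number of tests in the family, nor the alpha per test, nor the adjustment method.

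The abstract and the first hypothesis under Objectives {7} state the primary outcomes as two constructs: cardiorespiratory fitness and muscle strength. Outcomes {12} and Table 2 list the measures. They name "cardiorespiratory fitness measured with resting heart rate [35] and the heart rate recovery test [36, 37] as well as muscle strength", the last assessed by hand-held dynamometer, which makes three primary measures. Nothing in the article combines the two heart-rate measures, ranks them or makes one of them the lead. The primary analysis section mentions three families of hypotheses across primary and secondary outcomes without listing their members.

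**The concern.** A detectable effect under family-wise control depends on how many tests share the 0.05. If the calculation assumed one test per construct while the analysis has one test per measure, the printed power and the printed error rate describe a smaller family than the one in the outcome list.

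Two things are then at stake. With the error rate held at 0.05 over three tests by a single-step rule, power at 0.552 is below the claimed 80%. With each of the three measures tested at the alpha that 0.552 implies, the family-wise error is above 0.05. Leaving the role of the two heart-rate measures open would also allow either one to be presented as the cardiorespiratory result once the data are known.

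**Working it through.** **Inputs**
- Family-wise alpha 0.05 two-sided, power 80%, 82 completers, correlation 0.6, ANCOVA: Sample size {14}.
- 41 per arm: an assumption, inferred from the close balance between arms described under Sequence generation {16a}.
- Three primary measures: Outcomes {12} and Table 2. Two primary constructs: abstract and Objectives {7}.

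**Formula**

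The standard error of the adjusted difference, in SD units, is √(1 − ρ²) × √(1/41 + 1/41) = 0.8 × 0.2209 = 0.1767. Power at effect d comes from the noncentral t distribution with 79 degrees of freedom and noncentrality d / 0.1767. At d = 0.552 the noncentrality is 3.124.

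**Reproducing the plan's figure**

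| Tests in family | Alpha per test (Bonferroni) | Detectable d at 80% power | Power at d = 0.552 |
|---|---|---|---|
| 1 | 0.05 | 0.501 | 87.0% |
| 2 | 0.025 | 0.554 | 79.8% |
| 3 | 0.0167 | 0.582 | 75.0% |

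The Šidák alpha for two tests (0.0253) gives 0.553, and for three tests 0.581. Solving for the alpha at which 0.552 has exactly 80% power gives 0.0256. The stated figure therefore sits at a two-way split. The normal approximation places it there too: 0.495, 0.545 and 0.572 for one, two and three tests, with 76.7% power at 0.552 over three.

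**If all three measures were tested at 0.025**

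Family-wise error with independent tests is 1 − 0.975³ = 7.3%. By simulation it is about 7.0% at a correlation of 0.3 between measures and about 6.5% at 0.5. These correlations are assumptions, since the protocol gives none.

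**If three measures were tested with Holm at overall 0.05** (simulation, d = 0.552 wherever an effect is present)
- All three measures have the effect: power per measure is about 84% (independent), 83% (correlation 0.3), 82% (0.5) and 81% (0.8).
- Only one measure has the effect: about 75%, the same as Bonferroni.

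**Completers**

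108 × 0.75 = 81, while 82 completers means 26/108 = 24.1% attrition. With 81, the two-test detectable d rises by about 0.004.

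**The case against.** The strongest reply is that 0.552 agrees with how the protocol states its primary outcomes, as two constructs. The two-test split is an inference from arithmetic and is printed nowhere. The article says its families of hypotheses have been configured, so a rule for the two heart-rate measures may exist in a fuller document. This stands as a limit on what can be claimed. It does not remove the mismatch, because the outcome list in this article gives three separate measures, and a later document could make 0.552 right for single-step testing only by combining, ranking or dropping one.

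A reader might infer that 80% power at 0.552 and family-wise error 0.05 cannot both hold over three tests. The documents do not support that. They name no adjustment method, and under Holm the two can coexist when all three effects are about 0.552. What Holm does not do is guarantee 80% for a measure that is the only one with an effect.

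A reader might also infer that the trial will run at an inflated error rate. The protocol declares control at 0.05, and no section says each measure will be tested at 0.025, so the 6.5 to 7.3% is conditional. Nor does the text support counting dynamometry as more than one endpoint.

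Finally, a change-score analysis with a single test at 0.05 also gives about 0.553: √(2 × (1 − 0.6)) × (1.960 + 0.842) × √(4/82). That contradicts both the stated ANCOVA and the stated family, so it does not rescue the figure.

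**Conclusion.** The point holds in a bounded form. Under the stated ANCOVA and a single-step adjustment, 0.552 belongs to a family of two tests, while the protocol lists three primary measures with no composite or hierarchy. For three tests the detectable effect is 0.582 in place of 0.552, and power at 0.552 is about 75% in place of 80%. Under Holm that 75% is the floor, and power per measure is about 81 to 84% if every measure has the effect.

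The shortfall is modest: 0.03 SD, or about five points of power (about three by the normal approximation). It rests on equal arms, the stated correlation of 0.6 and three separately tested measures. The 81-against-82 discrepancy is a rounding matter and carries no weight in this conclusion.

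**What to change.** State the number of primary tests and the adjustment, and take one of two routes before outcome data are analysed.

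- **(a) Two primary tests.** Designate either resting heart rate or heart rate recovery as the cardiorespiratory primary measure, move the other to secondary, and keep a detectable d of about 0.55 with two tests at 0.025.
- **(b) Three primary tests.** Keep all three measures, name the adjustment (for example Holm at overall 0.05), and restate the detectable d guaranteed for any single measure as about 0.58. Say that power at 0.552 is about 75% in the worst case, where only one measure has an effect, so that the figure is not read as Holm's power in general.

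As a minor correction, give 81 completers with 25% attrition, or 24% attrition with 82.

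The cost is a change of wording. Route (a) gives up one measure's primary status, and route (b) prints a slightly less favourable detectable effect. Neither needs more participants.

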### Recruitment {15}

Potential participants will be primarily reached by disseminating recruitment information through local disability service providers, their social media outlets, and the study website (https://m2mstudy.org). If potential participants are interested in participating, they will be directed to the study website to complete an electronic pre-screening form linked to REDCap.

#### Concealment mechanism {16b}

The randomization sequence is uploaded to a randomization module in REDCap.

#### Implementation {16c}

Randomization will be performed entirely in REDCap by study staff after a participant completes baseline assessment.

### Assignment of interventions: blinding

#### Who will be blinded {17a}

Given the nature of the intervention, it is not plausible to blind participants and study staff who perform the randomization and monitor the intervention delivery. However, all data collection and analyses will be performed by study investigators and staff who are blinded to the study assignments.

#### Procedure for unblinding if needed {17b}

Study personnel who are responsible for collecting and analyzing data will remain blinded throughout the study period.

### Data collection and management

#### Plans for assessment and collection of outcomes {18a}

Before conducting the baseline teleassessments, study staff will connect with each participant for a virtual home visit via Zoom using the laptop mailed to them. The purpose of this visit is to walk participants through all provided testing equipment and identify places at home to exercise safely. The testing equipment includes a blood pressure monitor for measuring resting blood pressure and heart rate, a pulse oximeter for the heart rate recovery test, a hand dynamometer for the grip strength test, and two cones and a tape measure for the Short Physical Performance Battery and the Timed Up and Go tests.

All physical outcomes will be performed by assessors who are trained to administer the teleassessments via Zoom based on standardized protocols. All data from the teleassessments will be entered directly into REDCap. All self-report outcomes will be collected through electronic questionnaire packets delivered via REDCap. All items of the questionnaire packets are set as must-provide-value so participants are required to answer before submission to prevent data missingness. Each questionnaire packet is also set to be delivered to participants three times, separated by 3 days, if it is not completed. A follow-up phone call will be made if participants do not complete the packet after 7 days to ensure participants receive the packet and remind them to complete it within the next 3 days. Randomization will not take place until the the baseline teleassessments and questionnaire packet are completed.

#### Plans to promote participant retention and complete follow-up {18b}

Financial incentives will be provided to participants for completing study assessments, which include $25 for baseline and $50 for post 12-week intervention.

#### Data management {19}

All data will be collected remotely and will be entered directly and stored in REDCap. REDCap is a software program that was developed by Vanderbilt University, with collaboration from a consortium of institutional partners and the NIH National Center for Research Resources, for electronic collection and management of research and clinical trial data. All collected data will be systematically cleaned and verified. Data checking and cleaning involves secondary checks to identify any impossible values (e.g., 0 s to complete Timed Up and Go test) and univariate or multivariate outliers. Any erroneous data points will be corrected and the correction will be documented. REDCap data collection projects rely on a thorough study-specific data dictionary defined in an iterative self-documenting process by all members of the study team.

#### Confidentiality {27}

REDCap is 21 CRF Part 11 capable. Currently, REDCap installations support electronic signatures by positively identifying the user through a unique username and password combination. Access to the REDCap database will be given to the study personnel only, including the biostatistician and data management personnel. Data being analyzed will be exported in de-identified format. As part of the data dictionary development process, individual fields are denoted as “identifiers.” When exporting a de-identified dataset, these variables are omitted. Identities of participants will not be revealed in the presentation or publication of any result from this study. All study personnel are educated about the importance of strictly protecting participants’ rights to confidentiality and can only access the data necessary for job completion. Participants will be informed of law-mandated instances in which confidentially could be breached.

#### Plans for collection, laboratory evaluation, and storage of biological specimens for genetic or molecular analysis in this trial/future use {33}

Not applicable, no biological specimens will be collected in the study.

## Statistical methods

### Statistical methods for primary and secondary outcomes {20a}

#### Primary analysis

The primary analysis for the average treatment effect (**primary aim**) will employ an intent-to-treat linear mixed model ANCOVA with the baseline outcome measures as covariates, the corresponding post-intervention outcome measures as the dependent variables, the intervention as the main factor, and the intervention waves as random effect. In general, missingness will be handled by our choice of mixed models to handle the multi-level data. Mixed models use all the data available to directly estimate model parameters via maximum likelihood or restricted maximum likelihood. Where necessary, we will supplement these primary analyses by using multiple imputation procedures with 10 imputations [4]. We have configured three families of hypotheses based on our primary and secondary outcomes.

For the **secondary aim**, we will estimate the effect sizes and their 95% confidence intervals and compare them with the corresponding effect sizes and interval estimates from a previous M2M trial [65]. We will generate 95% percentile bootstrap confidence intervals between the differences in the effect sizes utilizing data from both trials. To test for pre-specified moderators, we will extend our models in the primary aim to include moderators as main effects along with an interaction term with the intervention. A test for interaction between the moderator and intervention will be conducted.

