### Interventions

Enrolled participants who complete baseline assessments will be randomly assigned to *eM2M* or *WC*. After randomization, participants in the *eM2M* arm will meet virtually with study staff who will provide information about the intervention schedule and an online program (e-STORIES) [29] on exercise self-regulation strategies, including goal setting, to be completed prior to beginning the intervention. Participants in *WC* will be instructed to maintain their usual activities during the 12-week intervention and will be invited to participate in an eM2M program after the control period. Both *eM2M* and *WC* participants will be asked to complete a weekly electronic survey on their physical activity level.

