### Intervention description {11a}

The eM2M intervention consists of three sessions per week for a total of 36 sessions over 12 weeks. The intervention provides three different programs based upon participants’ functional mobility, which are classified into: Group I (seated exercise only), Group II (seated and standing exercise with or without support while standing), and Group III (exercise for right and left side of the body).

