#### Components of the eM2M intervention

The eM2M intervention is highly structured to ensure strong fidelity between instructors. Each session consist of 7 to 8 movement routines accompanied with music. Every routine incorporates combinations of various movement patterns and sequences that target one of the four fitness components described below and can be adapted to the participants’ functional mobility level.

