### Strategies to improve adherence to interventions {11c}

The eM2M intervention is underpinned by four Social Cognitive Theory constructs: self-efficacy, self-regulation, outcome expectations, and social support [33]. Self-efficacy is targeted through (1) *mastery experience*: begin with lower exercise intensity and movement complexity and progress to higher exercise intensity and movement complexity across the intervention, to ensure that participants are challenged in a progressive manner; (2) *verbal persuasion*: motivate and encourage participants during class through verbal positive reinforcement; and (3) *emotional/physiological states*: ask participants to rate their RPE as well as pain and fatigue level at the beginning and end of each eM2M session to increase awareness of emotional and physiological states. Self-regulation and outcome expectations are addressed by asking participants to set monthly exercise goals and discuss expectations they have about exercise. In addition, the eM2M instructors will explain targeted outcomes to participants at the beginning of each routine. Social support is addressed by having group classes where participants with similar functional mobility levels are exercising together and by giving participants time at the beginning and end of each class to talk and interact with each other. The purpose of having gallery view on the Zoom platform at the beginning and end of each session is to facilitate the group interaction and social support. In addition, email or text reminders will be sent to participants a day before the intervention starts and one hour prior to each eM2M session.

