	Exercise self-regulation	Exercise Goal-setting Scale [60]	Baseline and 12 weeks
	Outcome expectations for exercise	Multidimensional Outcome Expectations for Exercise Scale [61]	Baseline and 12 weeks
	Social support for exercise	Social Provisions Scale [62]	Baseline and 12 weeks
**Moderators**	Functional mobility	Short Physical Performance Battery [41]	Baseline
	Disability type	Demographics and Health History Questionnaire	Baseline
**Covariates**	Barriers in physical activity	Barriers in Physical Activity Questionnaire [63]	Baseline

In addition, after participants complete the eM2M intervention, they will be asked to participate in semi-structured interviews via Zoom. The interviews will be conducted in a group format (the same group of participants that underwent the intervention together). The interviews will include questions that probe participants’ perceived impact of eM2M on their health and function, as well as their experience exercising with other participants with similar functional levels who have different disabilities. The interviews will be audio-recorded, transcribed, and analyzed using a latent thematic analysis approach (underpinned by interpretivism).

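### The primary model has a wave effect but no term for the eM2M exercise classes; if classmates' outcomes are correlated, its standard errors tend to be too small and the detectable d of 0.552 optimistic

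*Protocol article*

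**What the plan says.** - **Model.** Under Primary analysis, the post-intervention outcome is regressed on its baseline value with "the intervention as the main factor, and the intervention waves as random effect". The same paragraph says "missingness will be handled by our choice of mixed models to handle the multi-level data", but wave is the only level it names.
- **Delivery in the eM2M arm.** Under Intervention description {11a}, "The intervention provides three different programs based upon participants’ functional mobility", with 36 sessions over 12 weeks. Section {11c} describes social support as coming from "having group classes where participants with similar functional mobility levels are exercising together". Membership looks stable, because Outcomes {12} plans exit interviews with "the same group of participants that underwent the intervention together".
- **Control arm.** Under Interventions, waitlist participants "will be instructed to maintain their usual activities during the 12-week intervention". They have no class.
- **Waves.** Sequence generation {16a} balances the arms across waves within each stratum of 36, so each wave contains both arms.
- **Sample size {14}.** A detectable d of 0.552 is obtained from "an analysis of covariance (ANCOVA)-based approach" with 82 completers, a baseline-outcome correlation of 0.6, 80% power and a family-wise two-sided error of 0.05. No ICC or design effect is mentioned.

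**The concern.** This is a partially nested design, with grouping in the eM2M arm and none in the control arm. Because every wave contains both arms, a common wave intercept largely cancels from the treatment contrast. Class-to-class variation does not cancel. It exists on one side of the contrast only and adds to the true variance of the treatment estimate, while the stated model treats classmates as independent given wave.

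The design gives reason to expect some dependence. Classmates share sessions and time to interact, and group cohesion and instructor support are named as possible mediators. The primary aim covers the primary and secondary outcomes, and its models are extended for the moderator tests, so an understated standard error would carry through all of them. It would also weaken the family-wise 0.05 on which the sample size rests.

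**Working it through.** **1. Reproducing 0.552.** Inputs from Sample size {14}: 82 completers, correlation 0.6, 80% power. A 1:1 split (41 per arm) is assumed. With independent participants,

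d = (z for alpha/2 + z for power) × √(1 − 0.6²) × √(2/41).

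- Alpha 0.05: (1.960 + 0.842) × 0.8 × 0.2209 = 0.495.
- Alpha 0.05/2: (2.241 + 0.842) × 0.8 × 0.2209 = 0.545, or 0.554 with the t distribution.
- Alpha 0.05/3: 0.572.

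The stated 0.552 matches a two-way split of alpha with no design effect, so at that alpha it contains no allowance for clustering.

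**2. Effect of classes in one arm.** Let m be completers per class. The ICC is taken on the baseline-adjusted scale, with equal total variance in the two arms. The eM2M mean has its variance multiplied by 1 + (m − 1)ICC and the control mean does not. Hence

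true SE / independence SE = r = √[1 + (m − 1)ICC/2],

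detectable d = 0.552 × r, and approximate type I error = 2[1 − Φ(1.96/r)].

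The protocol gives neither m nor ICC. Assuming one class per programme in each wave, 2, 3, 5 or 6 waves give 6, 9, 15 or 18 classes, and m = 41 divided by that number.

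| Classes | m | ICC | r | Detectable d | Type I error, formula | Type I error, simulated |
|---|---|---|---|---|---|---|
| 6 | 6.8 | 0.01 | 1.014 | 0.560 | 5.3% | 5.1% |
| 6 | 6.8 | 0.05 | 1.070 | 0.591 | 6.7% | 6.8% |
| 6 | 6.8 | 0.10 | 1.136 | 0.627 | 8.4% | 8.7% |
| 9 | 4.6 | 0.01 | 1.009 | 0.557 | 5.2% | 5.2% |
| 9 | 4.6 | 0.05 | 1.044 | 0.576 | 6.0% | 5.5% |
| 9 | 4.6 | 0.10 | 1.086 | 0.600 | 7.1% | 7.7% |
| 15 | 2.7 | 0.01 | 1.004 | 0.554 | 5.1% | 4.8% |
| 15 | 2.7 | 0.05 | 1.021 | 0.564 | 5.5% | 5.4% |
| 15 | 2.7 | 0.10 | 1.042 | 0.575 | 6.0% | 6.3% |
| 18 | 2.3 | 0.01 | 1.003 | 0.554 | 5.1% | not run |
| 18 | 2.3 | 0.05 | 1.016 | 0.561 | 5.4% | not run |
| 18 | 2.3 | 0.10 | 1.032 | 0.570 | 5.7% | not run |

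**3. Does adjusting for wave remove it?** The simulated column comes from 8,000 trials per cell with 82 completers, baseline slope 0.6, class effects in one arm, and ANCOVA adjusted for wave by fixed terms. The Monte Carlo standard error is about √(0.05 × 0.95/8000) = 0.24 points. At ICC 0 the error was 5.0-5.1%, so the excess comes from the classes, and wave adjustment does not remove it.

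A further wave-adjusted simulation gave 6.6% and 8.9% (ICC 0.05 and 0.10) with 2 waves, 6.2% and 7.5% with 3, and about 5-6% with 5-6 waves. A random wave intercept fitted by REML (2,000 trials per cell) gave 6.2% and 8.8% with 6 classes, 6.9% and 7.5% with 9, and about 6% with 18. Differences of half a point between runs should not be read closely.

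**The case against.** A reader might infer that the standard errors are too small as a matter of fact, by several points of type I error. The documents do not support that, for three reasons.

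- **The ICC could be near zero.** The primary outcomes are resting heart rate, heart rate recovery and dynamometer strength, all adjusted for baseline. Participants exercise at home, muted during the routines, and "The eM2M intervention is highly structured to ensure strong fidelity between instructors". Naming group cohesion as a possible mediator does not establish a material class correlation in heart rate or grip. At ICC 0.01 the error is close to nominal in every layout tried.
- **The larger figures need few, large classes.** Trial status puts the first wave in March 2021 and the end of recruitment in July 2022, about 70 weeks. With 12-week waves, 70/12 = 5.8, so 5-6 consecutive waves fit. That points to 15-18 classes of 2.3-2.7 completers, where the excess is at most about one point. The wave count is not stated, so this is also inference.
- **There is an opposing error.** Randomisation is stratified by functional mobility group, but the stated model does not list that factor. If strata differ after baseline adjustment, leaving it out inflates the model standard error. With an assumed 0.3 SD step between strata, simulated type I error at ICC 0.05 and 0.10 was 4.2% and 5.3% (5 waves), 5.0% and 5.9% (3 waves), and 5.0% and 6.9% (2 waves).

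All three points stand as limits on size and certainty. They do not rescue the variance structure: a shared wave intercept still cannot represent variance present in one arm, and an accidental offset is no reason to rely on it. Nor is this a detail left for an analysis plan, because the protocol states the random part of its primary model.

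**Conclusion.** The concern holds conditionally. The stated model omits a source of variance that the design can create in the eM2M arm only. If the class ICC is positive, inference tends to be anti-conservative and the detectable d is above 0.552.

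For an ICC of 0.01-0.10 the plausible size runs from negligible (15-18 small classes, or ICC 0.01 in any layout) to moderate (6 classes, ICC 0.05-0.10). The net direction is not certain while the stratification factor is also absent from the stated model. These sizes assume 41 completers per arm, one class per programme in each wave, and equal total variance in the two arms.

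This should be fixed before analysis, with medium confidence that it matters in practice. It does not show that the trial's error rate is in fact inflated, and 0.552 is not an arithmetic mistake.

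**What to change.** Under Primary analysis:

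- Add a random intercept for eM2M class that applies in the eM2M arm only, with waitlist participants entered as singletons carrying no class variance. Define class by assignment, so that the intent-to-treat comparison is kept.
- Keep wave, and add functional mobility stratum as a fixed effect.
- Use Kenward-Roger or Satterthwaite degrees of freedom.
- Treat arm-specific residual variances as optional, because they are weakly identified when classes are small.

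For the secondary-aim bootstrap, resample whole classes in this trial's eM2M arm. Under Sample size {14}, restate the detectable difference over an ICC range of 0.01-0.10 with the expected class size.

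The change affects the analysis only. It needs a class identifier, which scheduling should already produce, and leaves recruitment, visits and delivery as they are. The cost is slightly wider intervals and fewer degrees of freedom. With classes of two or three completers the class variance may be estimated at zero, and the plan should say in advance how that will be handled.

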### Criteria for discontinuing or modifying allocated interventions {11b}

There are no criteria for discontinuing or modifying allocated Intervention when requested by participants. Participants may choose to stop the intervention or withdraw from the study for any reason, including being assigned to a study arm that is not a preference.

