### Methods in analysis to handle protocol non-adherence and any statistical methods to handle missing data {20c}

Missing data will be imputed using multiple imputation where necessary, with assumption that the missingness mechanism is missing at random.

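### The primary mixed model cannot handle missing 12-week outcomes: as specified it is a complete-case ANCOVA under an intent-to-treat label

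*Protocol article*

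**What the plan says.** The Primary analysis section of the protocol article specifies a "linear mixed model ANCOVA with the baseline outcome measures as covariates, the corresponding post-intervention outcome measures as the dependent variables", with "the intervention as the main factor, and the intervention waves as random effect". It calls this analysis intent-to-treat.

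On missing data the same section says: "In general, missingness will be handled by our choice of mixed models to handle the multi-level data". The reason given is: "Mixed models use all the data available to directly estimate model parameters via maximum likelihood or restricted maximum likelihood". Imputation comes second: "Where necessary, we will supplement these primary analyses by using multiple imputation procedures with 10 imputations". The item on missing data {20c} adds: "Missing data will be imputed using multiple imputation where necessary, with assumption that the missingness mechanism is missing at random". Neither place says what makes imputation necessary.

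Under Outcomes {12}, the primary and secondary outcomes "will be assessed at baseline and post 12-week intervention", with no assessment in between. Under Plans for assessment and collection of outcomes {18a}, randomisation waits until the baseline assessments and questionnaires are complete. Sample size {14} plans for 25% attrition, with 82 participants finishing.

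**The concern.** A likelihood-based mixed model helps with missing data when a person contributes several responses and some are observed: the observed ones carry information about the missing ones. Here each person has one response per outcome. Baseline is complete by design, so the gaps fall on that one response. The protection that the plan claims is then absent.

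At stake is the primary estimate. About a quarter of those randomised would be left out of an analysis presented as intent-to-treat, and the plan's text would reassure readers that their absence had been dealt with. The trial is unblinded for participants and the control arm is a waitlist, so reasons for missing the 12-week assessment could differ between arms and could be related to outcome.

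**Working it through.** **1. The plan's own figure.** Inputs from Sample size {14}: N = 82 completers, correlation ρ = 0.6, 80% power, two-sided family-wise error 0.05. Equal allocation is assumed. The detectable difference is

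MDD = (z[1−α/2] + z[0.80]) × √(4(1 − ρ²)/N).

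With α = 0.05/2 = 0.025: (2.241 + 0.842) × √(4 × 0.64/82) = 3.083 × 0.1767 = 0.545. The noncentral t version gives 0.554. The stated 0.552 lies between them, so it reproduces with the error rate split over two primary outcomes. It already counts completers only.

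**2. Who enters the model.** For participant i in wave w the stated model is

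y(12 wk) = β0 + β1 × baseline + β2 × arm + u(w) + e(i).

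There is no participant-level random effect and no second response. If y(12 wk) is missing, the likelihood has no term for that person; the wave effect is shared and recovers nothing individual. At the planned attrition 108 − 82 = 26 participants (24%) contribute nothing.

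**3. Numerical check.** A trial was simulated with 108 participants in six waves, ρ = 0.6 and 26 missing 12-week values, and the stated model was fitted. It used 82 records. Replacing the 26 dropouts' baseline values by an absurd number left the treatment estimate at 0.6446, unchanged.

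**4. When this biases the estimate.** Let p1 and p0 be the proportions missing in eM2M and waitlist. Let δ1 and δ0 be the dropout-minus-completer gaps in the 12-week outcome that remain after adjustment for baseline, in outcome SD. Then

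bias ≈ −p1δ1 + p0δ0.

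The documents give none of the gaps and no dropout by arm, so these are assumptions:

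| p1 | δ1 | p0 | δ0 | Bias (SD) |
|---|---|---|---|---|
| 0.25 | 0 | 0.25 | 0 | 0 |
| 0.25 | −0.3 | 0.25 | 0 | +0.075 |
| 0.25 | −0.3 | 0.25 | −0.3 | 0 |

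The middle row is 0.075/0.552 = 14% of the detectable difference.

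**5. Large-sample simulation.** The true effect was zero, about 27–28% of outcomes were missing overall, and waitlist dropout was random in the second and third cases. The mechanisms are assumed.

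- Dropout depends only on baseline and arm: bias about 0.00 SD.
- eM2M dropout depends on the 12-week outcome itself: +0.16 SD.
- eM2M dropout depends on a post-randomisation variable, such as adherence, correlated 0.5 with the residual outcome: +0.14 SD.

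**The case against.** The strongest reply is that recovering no information is not the same as being biased. If missingness depends only on arm and baseline, the complete-case likelihood is the observed-data likelihood and ML or REML is valid. That is a missing-at-random condition, and {20c} assumes missing at random. This stands: the plan is wrong about what the model does for missing data, but not necessarily wrong in its estimate. However, the condition the model needs is narrower than missing at random given everything collected. The third case in the simulation could be missing at random once adherence is used, yet this model does not use it.

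A second reply is that multiple imputation is already planned, and that its details belong in a statistical analysis plan. The details do. The protocol itself, however, assigns the main task to the mixed model and makes imputation a conditional supplement, so the primary estimate as written remains the complete-case one. Imputation from arm and the same baseline alone would also target the same quantity as the ANCOVA; any gain must come from auxiliary variables.

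Three stronger readings are tempting but not supported:

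- A reader might infer that the plan expects preference-driven dropout, because under {11b} participants may "withdraw from the study for any reason, including being assigned to a study arm that is not a preference". That states a right. The 25% attrition has no stated cause and no split by arm.
- A reader might infer that everyone who stops the sessions is lost. {11b} separates stopping the intervention from withdrawing from the study. Anyone assessed at 12 weeks stays in the model.
- A reader might infer that the trial is underpowered for this reason. It is not, since 0.552 rests on 82 completers.

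**Conclusion.** The statement that the mixed model handles missingness is wrong for the model specified. As written, the primary analysis is a complete-case ANCOVA on about 82 of 108 randomised participants, and the intent-to-treat label does not describe it. The estimate is valid only if, given arm and that outcome's baseline, missingness is unrelated to the 12-week outcome.

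The documents do not show that the estimate will be biased, or by how much. The 0.075 SD is an illustration that needs three assumptions together: 25% dropout in eM2M, a residual gap of 0.3 SD there, and no gap in the waitlist arm. A raw gap of 0.3 SD would matter less where baseline explains part of it, and a similar pattern in the waitlist arm would cancel it. The detectable difference needs no revision.

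**What to change.** 1. Delete the statement that the mixed model handles missingness.
2. In both the Primary analysis section and {20c}, replace the conditional wording with a firm commitment to multiple imputation, by arm, of all randomised participants for the primary outcomes. Use auxiliary data the trial already collects: baseline values of the other outcomes, functional mobility group, diagnosis, the weekly physical activity surveys as far as available, and attendance in the eM2M arm.
3. Report the ANCOVA on observed 12-week values alongside it, labelled as complete-case.
4. Add one delta-adjusted sensitivity analysis in which the imputed outcomes of dropouts are shifted separately by arm.

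The cost is a change of wording and modest extra programming, with no new data collection. The gain will be limited if the weekly surveys and attendance records stop when a participant withdraws, because the auxiliary information is then thinnest for the people whose outcomes are missing. The delta-adjusted analysis is there for that case.
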